## Abstract

**Background:**

Nucleos(t)ide analogues (NAs) are the first-line option against chronic hepatitis B (CHB). NAs produce potent suppression of viral replication with a small chance of HBsAg seroclearance and a high risk of virological relapse after discontinuation. The combined therapy of NAs plus traditional Chinese medicine (TCM) is widely accepted and has been recognized as a prospective alternative approach in China. Based on preliminary works, this study was designed to observe the therapeutic effect of TCM plus entecavir (ETV) against HBeAg-positive chronic hepatitis B with respect to reducing the recurrence risk after NA withdrawal.

**Methods/design:**

The study is a nationwide, multicenter, double-blind, randomized, placebo-controlled trial with a duration of 120 weeks. A total of 18 hospitals and 490 eligible Chinese HBeAg-positive CHB patients will be enrolled and randomly allocated into the experimental group and control group in a 1:1 ratio. Patients in the experimental group will be prescribed TCM formulae (Tiaogan-BuXu-Jiedu granules) plus ETV 0.5 mg per day for consolidation therapy for 96 weeks. Patients in the control group will be prescribed TCM granule placebo plus ETV 0.5 mg per day for the same course. After consolidation therapy, all patients will discontinue their trial drugs and be closely monitored over the next 24 weeks. Once clinical recurrence (CR) occurs, ETV treatment will be restarted. The primary outcome is the cumulative rate of CR at the end of this trial.

**Conclusion:**

This study is the first of its kind to observe therapeutic effects with respect to reducing recurrence after NA withdrawals after unified integrative consolidation therapy in the CHB population.

**Trial registration:**

Chinese Clinical Trial Registry No. ChiCTR1900021232. Registered on February 2, 2019

Chronic hepatitis B (CHB) has been one of the most concerning diseases worldwide. Every year, approximately 1 million people die of CHB-related cirrhosis and hepatocellular carcinoma [1]. Nucleos(t)ide analogues (NAs) therapy is widely applied in patients with chronic hepatitis B virus (HBV) infection. Currently, six NAs are available against CHB: lamivudine, telbivudine, entecavir (ETV), adefovir, tenofovir disoproxil fumarate (TDF), and tenofovir alafenamide (TAF), of which ETV and TDF are recommended as first-line therapies [2–4]. NAs inhibit the reverse transcriptase activity of the HBV polymerase and thus suppress viral replication. However, NAs exert little effect on viral covalently closed circular DNA (cccDNA) in the nucleus [5]. Hence, they cannot permanently eradicate the virus. Currently, hepatitis B surface antigen (HBsAg) loss is the most widely accepted endpoint to guide cessation of NA treatment. However, as HBsAg loss is an infrequent event, this strategy entails an indefinite therapeutic duration that could be lifelong for the vast majority of NA-treated patients [6]. Therefore, the benefit of long-term treatment should be weighed against the burden of life-long medication, monitoring, and adherence. In addition, the long-term risk for the development of resistance and adverse events (AEs) remains unclear.

In recent years, some scholars have attempted to find approaches for preventing relapses after NAs withdrawal [7–9]. A previous study observed the outcomes after the cessation of ETV therapy among patients who fulfilled the stopping rules of the Asia-Pacific Association for the Study of the Liver (APASL) [10]. The 2-year cumulative rates of virological and clinical relapse were 41.3% and 33% in hepatitis B e antigen (HBeAg)-positive patients, and the 3-year cumulative rates of virological and clinical relapse were 62.7% and 48.3% in HBeAg-negative patients, respectively. The risk after discontinuation of the therapy is concerning.

Traditional Chinese medicine (TCM) therapy has a long history and definite curative effect for treating various chronic liver diseases including chronic hepatitis and fibrosis/cirrhosis [11–13], and abundant data and experience have accumulated in long-term clinical practice and scientific research. Although TCM therapy alone has no explicit antiviral effect, it has some advantages in improving clinical symptoms [14], alleviating liver inflammation, anti-fibrosis [15], and regulating immune function [16]. In China, supported by major national special research projects funded by the Ministry of Health, some research results have been obtained regarding the treatment of chronic hepatitis B by the combination of TCM and NAs, the advantages of TCM therapy in the treatment of chronic hepatitis B have been preliminarily clarified [17], an integrated TCM and NAs therapeutic schedule has been developed [18], and it has been proven that the combination of TCM and NAs can significantly enhance the negative conversion ratio of HBeAg, including that seen in refractory diseases [19, 20]. Based on the preliminary work, this study carries out research on combination TCM and NAs strategies for HBeAg-positive chronic hepatitis B. Through a national multicenter double-blind, randomized controlled study, we will verify the effect of combination TCM and NA therapy in reducing the recurrence rate after drug withdrawal.

## Registration

We had registered this trial before recruitment on the Chinese Clinical Trial Registry (No. ChiCTR1900021232). This trial will be conducted following the principles of the Declaration of Helsinki (2004 version). The study protocol has been approved by the Ethics Committee of Dongzhimen Hospital affiliated to Beijing University of Chinese Medicine before recruitment (Approval number: DZMEC-KY-2018-61).

## Recruitment

A total of 490 patients will be recruited by nineteen clinical centers in China nationwide listed as follows: Dongzhimen Hospital affiliated to Beijing University of Chinese Medicine, Shenzhen Traditional Chinese Medicine Hospital, Guangdong Hospital of Traditional Chinese Medicine, Liaoning Hospital of Traditional Chinese Medicine, the First Affiliated Hospital of Guangxi University of Chinese Medicine, Shaanxi Hospital of Traditional Chinese Medicine, Mengchao Hepatobiliary Hospital of Fujian Medical University, Beijing Chinese Medicine Hospital, Beijing Ditan Hospital, Chongqing Traditional Chinese Medicine Hospital, Affiliated traditional Chinese medicine hospital of Southwest Medical University, Shanghai Shuguang Hospital, the Sixth People’s Hospital of Shenyang, 302 Military Hospital of China (the Fifth Medical Center of People’s Liberation Army of China), Shandong Hospital of Traditional Chinese Medicine, the Second People’s Hospital of Tianjin, Public Health Clinical Center of Chengdu, the Third People’s Hospital of Shenzhen, and the Second Hospital of Shandong University. We will recruit volunteers from the outpatient department of the hospitals.

The principal investigators (PIs) of subcenters will introduce the protocol as well as the benefits and risks of the study to the participants before enrollment. In the informed consent form, participants will be asked if they agree to allow the use of their data should they choose to withdraw from the trial. Participants will also be asked for permission for the research team to share relevant data with people from the universities taking part in the research or from regulatory authorities, where relevant. This trial does involve collecting biological specimens for storage. There is no anticipated harm from or compensation for trial participation.

The inclusion and exclusion criteria are listed below. The criteria for premature withdrawal from the study include protocol deviation, pregnancy, or investigator discretion.

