## Inclusion criteria

The inclusion criteria are as follows: (1) diagnosed CHB with positive HBeAg, who has experienced HBeAg clearance and/or seroconversion; (2) aged between 18 and 65; (3) TBIL < 3 × ULN; (4) HBsAg < 5000 IU/ml; (5) TCM symptoms are classified as stagnation of the liver and deficiency of Spleen Qi and Damp-Heat in the liver and gallbladder; and (6) voluntarily sign informed consent.

In the informed consent form, we explain the protocol and clearly inform the participants that after 96 weeks of consolidation therapy, they will stop NA treatment and be closely monitored for the next 24 weeks. Although the procedure complies with the AASLD [21], APASL [22], and EASL [23] guidelines for CHB treatment, there could be potential risks (including virological or clinical relapse) during the off-therapy period, and patients may be required to restart antiviral therapy. Patients are free to quit the trial any time before the off-therapy period.

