## Interviews

From the first day to the observation point of week 96, we will follow up patients every 24 weeks (± 3 days) and dispatch trial drugs on each visit. In addition, we will retrieve the empty boxes and the remaining doses of each patient for verification and recording. At the end of week 96, patients will be informed again about the potential risks of stopping NA therapy, and additional consent to participate in off-therapy observation will be required. From week 96 to week 120, we will set the intervals between interviews to 4 weeks (± 3 days).

Specimens collected during the trial will be stored in the Biobank of Dongzhimen Hospital. The specimens will be used to reconfirm the readings of existing assessments if necessary, as well as for genetic or molecular analysis in current trials and for future use in ancillary studies.

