## Primary outcomes

The primary outcome will be the incidence of recurrence after ETV withdrawal. Clinical recurrence is defined as a serum aminotransferase (ALT) over twofold of the upper limit of normal (ULN) while the HBV DNA > 2000 IU/mL.

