## Statistics analysis

An independent statistical committee will be in charge of the analysis. The statistical analysis team will conduct the intention-to-treat (ITT) analysis for the primary outcome, where all randomized populations will be included in the full analysis set (FAS). Subjects who violated the protocol will be inspected individually. The last observation carried forward method will be used to impute missing data.

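### Protocol deviation is a ground for leaving the study, which undercuts the all-randomised analysis and the off-therapy checks; separately, the stated freedom to quit ends when the off-therapy period begins

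*Protocol article*

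**What the plan says.** **Leaving the study.** Recruitment: "The criteria for premature withdrawal from the study include protocol deviation, pregnancy, or investigator discretion". The sentence does not say which deviations count or in which phase it applies, and it does not distinguish the study from the study drug. No section of the article keeps a withdrawn patient under follow-up.

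**Endpoint and its measurement.** Primary outcomes: "The primary outcome will be the incidence of recurrence after ETV withdrawal". Recurrence is judged on ALT together with HBV DNA. Table 1 schedules both (ALT under liver functions) every 4 weeks off therapy, from week 4 to week 24. Under Therapeutic regimen, confirmed recurrence in that period leads to antiviral treatment being restarted.

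**Analysis.** Statistics analysis commits to intention-to-treat for the primary outcome: "all randomized populations will be included in the full analysis set (FAS"). It adds that violators are looked at one by one. Missing data says that a case with incomplete off-therapy ALT or HBV DNA is left out of the primary analysis. Data management and quality control says that investigators record deviations on a breach report form within the CRF.

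**Quitting.** Inclusion criteria, describing the consent form: "Patients are free to quit the trial any time before the off-therapy period". The sentence before it warns that "there could be potential risks (including virological or clinical relapse) during the off-therapy period". Recruitment, with no phase limit, says "participants will be asked if they agree to allow the use of their data should they choose to withdraw from the trial". Interviews says of week 96 that "additional consent to participate in off-therapy observation will be required".

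**The concern.** Protocol deviation happens after randomisation and may be related to adherence, tolerability or prognosis. Using it to end a patient's participation has two consequences.

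- **Analysis.** The endpoint exists only off therapy, so a patient who leaves before or during that phase has no complete endpoint. The comparison then rests on those who stayed, not on those randomised.
- **Surveillance.** A patient who has just stopped entecavir leaves the trial's scheduled ALT and HBV DNA checks, in the phase where the article itself places the relapse risk.

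The quit sentence raises a different matter. Read as written, it states a participant's freedom to leave only up to the start of the phase with the named risk. At stake there is the validity of consent, not the data.

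**Working it through.** **Step 1. Follow a withdrawn patient through the sections.**

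- *Withdrawn for a deviation during consolidation (weeks 0 to 96).* The patient has no off-therapy ALT or HBV DNA. Under Missing data the case is out of the primary analysis. Under Statistics analysis it should be in.
- *Withdrawn for a deviation after entecavir stops.* The remaining 4-weekly checks end and the off-therapy data are incomplete. The conflict is the same, and trial surveillance is also lost.
- *Deviation recorded, patient kept.* The visits continue, the endpoint is observed, and the two analysis sections do not collide for this patient.

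The conflict therefore comes from two rules together: removal from the study, then exclusion for incomplete data. Statistics analysis also names last observation carried forward for missing data in general. I take the specific rule under Missing data to govern the primary outcome. Individual inspection of violators cannot recover results that were never collected.

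**Step 2. What the loss would cost, for scale only.**

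Inputs from Sample size estimation: 32% recurrence, a 12-point difference, 80% power, alpha 0.05, 245 per group, 20% loss. Two-sided testing is from Outcome analysis. The direction (32% versus 20%) is my assumption.

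n = [1.96 × √(2 × 0.26 × 0.74) + 0.8416 × √(0.32 × 0.68 + 0.20 × 0.80)]² / 0.12² = (1.2158 + 0.5172)² / 0.0144 ≈ 208.6, so 209 evaluable per group.

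The stated 245 is close to 209 × 1.2 = 251 (within 3%). Dividing instead, 209 / 0.8 gives 262. How loss was allowed for is a separate matter and does not affect this point.

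Power for 32% versus 20% under assumed total loss from 245 per group:

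| Assumed loss | Evaluable per group | Power |
|---|---|---|
| 20% (planned) | 196 | 77.5% |
| 25% | 184 | 74.9% |
| 30% | 172 | 72.0% |
| 40% | 147 | 65.1% |

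The article does not say whether withdrawals for deviation are inside the 20%.

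Bias, again as an assumption: let both arms truly relapse at 32%, and let a fraction f of relapsers be excluded in one arm only. The observed rate in that arm is 0.32(1 − f) / [0.32(1 − f) + 0.68].

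- f = 0.1: 0.288 / 0.968 = 29.8%, a false difference of 2.2 points.
- f = 0.2: 0.256 / 0.936 = 27.4%, a false difference of 4.6 points.

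The target difference is 12 points. Exclusion in one arm only is an extreme case. Equal exclusion in both arms would not create a difference under the null.

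**Step 3. The quit sentence.**

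Recruitment foresees participants who choose to leave and sets no phase limit. Inclusion criteria states the freedom to leave only for the time before the off-therapy period. The week-96 consent in Interviews gives a fresh choice about entering off-therapy observation, but does not say that a patient who enters may leave later. No other section says so either. Read literally, the sentence keeps patients in, so it does not add to the loss in Step 2.

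**The case against.** The strongest reply is that this is one line in a condensed article. The list is introduced as what the criteria include, and the full protocol may grade deviations and describe follow-up after withdrawal. The breach report form and the individual inspection of violators suggest recording and case-by-case review, not automatic removal. Retaining a withdrawn patient in the full analysis set is not in itself contradictory. Allocation is concealed from research personnel, so removal that favours one arm by choice is unlikely. The week-96 consent suggests that the quit sentence was meant to describe the opt-out before entecavir stops.

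Much of this stands as a limit on the point:

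- A reader might infer that any small deviation, such as an off-therapy visit outside the 3-day tolerance, leads to removal. The article does not say so. The term is unqualified, but how sites would apply it is unknown.
- A reader might estimate how many patients would have at least one late visit and set that beside the 20% loss allowance. That would count late visits under an assumed rate, not withdrawals or lost endpoints.
- A reader might infer that pregnancy outcomes go uncollected because pregnancy is also on the list. The article is silent, and a condensed article's silence does not show it.
- A reader might take the quit sentence as a further cause of lost data. On its wording it retains patients.

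The core is not answered. The article does more than omit detail: it names deviation as a ground for leaving the study, and it excludes cases with incomplete off-therapy data while promising an all-randomised analysis. Blinding limits selective removal but does not make a post-randomisation exclusion harmless. The likely intention behind the quit sentence does not change what participants would read.

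**Conclusion.** The point holds as two separate defects.

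1. Withdrawal from the study for protocol deviation, followed by exclusion for incomplete off-therapy data, conflicts with the stated intention-to-treat analysis. Where it happens after entecavir stops, it also ends the trial's surveillance of that patient. The size cannot be computed from the documents. The power and bias figures above show only what given amounts of loss would do. They rest on assumed loss rates, on 32% versus 20%, and, for the bias, on exclusion in one arm only.
2. The quit sentence is a consent defect. It is inconsistent with the unrestricted wording in Recruitment and is not repaired by the week-96 consent.

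The documents do not support a claim that patients will be removed for trivial deviations, or any predicted percentage of removals.

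**What to change.** **Exit rule.** In Recruitment, separate stopping study drug from leaving the study, and delete protocol deviation as a ground for leaving. Record deviations on the existing breach report form. With their consent, keep these patients in scheduled visits and endpoint collection to week 120. Reconcile Recruitment, Statistics analysis and Missing data, so that one rule says how randomised patients with incomplete off-therapy ALT or HBV DNA enter the primary analysis.

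**Consent wording.** In Inclusion criteria and the consent form, state that participants may withdraw at any time, including during off-therapy observation, and repeat this in the week-96 consent. Ask those who leave for permission to collect their remaining ALT and HBV DNA results.

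**Cost.** A wording amendment to the protocol and consent form, sent to the funder, the ethics committee and the sites as Protocol amendments already provides. The downside is small: some extra follow-up visits for patients who would otherwise have been withdrawn.

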## Inclusion criteria

The inclusion criteria are as follows: (1) diagnosed CHB with positive HBeAg, who has experienced HBeAg clearance and/or seroconversion; (2) aged between 18 and 65; (3) TBIL < 3 × ULN; (4) HBsAg < 5000 IU/ml; (5) TCM symptoms are classified as stagnation of the liver and deficiency of Spleen Qi and Damp-Heat in the liver and gallbladder; and (6) voluntarily sign informed consent.

In the informed consent form, we explain the protocol and clearly inform the participants that after 96 weeks of consolidation therapy, they will stop NA treatment and be closely monitored for the next 24 weeks. Although the procedure complies with the AASLD [21], APASL [22], and EASL [23] guidelines for CHB treatment, there could be potential risks (including virological or clinical relapse) during the off-therapy period, and patients may be required to restart antiviral therapy. Patients are free to quit the trial any time before the off-therapy period.

## Exclusion criteria

Any of the following cases will be excluded: (1) diagnosed with chronic hepatitis caused by non-viral causes, overlapped virus infections, or cryptogenic hepatitis; (2) accompanied by liver failure, hepatocirrhosis (including stage 4 fibrosis), hepatic encephalopathy, electrolyte disorders, gastrointestinal bleeding, fatal infections, or any other severe complications; (3) diagnosed with malignant tumors or with a progressive elevation of serum tumor markers; (4) diagnosed with primary or secondary cardiovascular, cerebrovascular, pulmonary, renal, endocrine, nerve, and hematology diseases; (5) participating or participated in other clinical trials within 1 month; (6) diagnosed mental disorders; (7) confirmed hepatitis B virus pre-C/C or P gene variants; (8) pregnant or lactating women, individuals that are scheduled to conceive or fertilize; and (9) with other unfavorable conditions.

## Sample size estimation

We calculated the sample size with PASS software (NCSS, LLC. Utah, USA. Version 15.0.5). Referencing a study published in 2016, in which the recurrence rate was 32% in HBeAg positive CHB patients after NA withdrawal within 24 weeks [24], we determined that we would need to achieve 80% power to detect a difference between the group proportions of 12%. The required significance level was set to 0.05. We set the sample size to 245 for each group, 490 in total, for which a 20% loss of participants was considered.

## Study drugs

The experimental drug (TCM granules) is Tiaogan-Buxu-Jiedu (TGBXJD) granules. All patients will be randomized to treatment with TGBXJD granules (orally, one dose per day) plus entecavir (ETV 0.5 mg per day) or TGBXJD granule placebo plus ETV. TGBXJD granules (including placebo formulations, 30 g per dose) will be provided by PuraPharm Co. Ltd., China (lot No. A190069710). The manufacturing procedures are as follows: every herb (*Bupleurum*, *Atractylodes* rhizomes, and *Scutellaria* root) will be extracted with 97 ± 2 °C water. The extract will then be filtered through 200 μm mesh filter cloth, and the filtrate will be concentrated under a vacuum to a relative density of 1.10~1.20 (temperature 60 ± 5 °C). The concentrate will be mixed after stirring for 30 min. The herbal granules will be collected with the dry granulation method. ETV tablet (0.5 mg per tablet) will be provided by CHIATAI TIANQING company, China (lotNo. 181214101, 181203201, 181024101). The major ingredients of TGBXJD are *Scutellaria*, *Bupleurum*, and *Atractylodes*.

## Therapeutic regimen

Patients who meet the inclusion criteria will be allocated in a 1:1 ratio to either the experimental group (EG) or the control group (CG). Patients in the EG will receive TGBXJD granules along with ETV. Patients in the CG will receive TCM placebo along with ETV. The treatment duration is 96 weeks. Those who develop clinical relapse during consolidation therapy (in the first 96 weeks) will be switched to TDF (300 mg per day) according to the guidelines [25] and be removed from the study. All patients who meet the following NA withdrawal criteria in the first 96 weeks will stop their ETV treatment and will be closely monitored in the following 24 weeks: (1) serum ALT persistently within the normal range (under 40 IU/L) and (2) serum HBV DNA persistently undetectable (under 30 IU/mL). Once clinical recurrence is confirmed during the off-therapy period, antiviral treatment (entecavir, 0.5 mg per day) will be restarted immediately (Fig. 1).

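### Analysis of all randomised patients is promised, but the primary outcome can be observed only in patients who pass several post-randomisation filters

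*Protocol article*

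**What the plan says.** All references are to the protocol article.

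- **Outcome.** Primary outcomes: "The primary outcome will be the incidence of recurrence after ETV withdrawal". Outcome analysis compares the proportions with off-therapy relapse by Pearson chi-square.
- **Analysis set.** Statistics analysis states an intention-to-treat analysis with every randomised patient in the full analysis set, and imputation by last observation carried forward (LOCF).
- **On-treatment relapse.** Therapeutic regimen: patients with clinical relapse during the 96 weeks of consolidation are switched to another antiviral "according to the guidelines [25] and be removed from the study".
- **Who stops.** Therapeutic regimen: "All patients who meet the following NA withdrawal criteria in the first 96 weeks will stop their ETV treatment", the criteria being persistently normal ALT and undetectable HBV DNA. The abstract says instead: "After consolidation therapy, all patients will discontinue their trial drugs".
- **Second consent.** Interviews, at week 96: "additional consent to participate in off-therapy observation will be required".
- **Other withdrawals.** Recruitment: "The criteria for premature withdrawal from the study include protocol deviation, pregnancy, or investigator discretion".
- **Incomplete data.** Missing data excludes from the primary analysis any case whose off-therapy ALT or HBV DNA is incomplete. It keeps LOCF for gaps that affect only secondary or safety analyses.

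**The concern.** Up to 96 weeks of randomised treatment pass before anyone is at risk of the primary outcome. Whether a patient reaches that point depends on ALT, HBV DNA, willingness to re-consent and staying in the study, and the assigned treatment can influence each of these. ALT and HBV DNA decide who may stop and also define relapse. The introduction credits traditional Chinese medicine with alleviating liver inflammation, so an effect on who qualifies is plausible.

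If the arms differ in who is filtered out, patients who stop in one arm are not comparable with those who stop in the other. An arm with more failures during consolidation can enter the off-therapy phase with fewer high-risk patients and look better. An arm that keeps more marginal patients can look worse. Because relapsers leave the study, an analysis plan written later cannot recover their outcomes.

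**Working it through.** **1. The plan's own figure.** Inputs from Sample size estimation: control recurrence 32% within 24 weeks of withdrawal, difference 12 points (read as 32% vs 20%), power 80%, 20% loss, and "The required significance level was set to 0.05" (two-sided in Outcome analysis). Mean proportion (0.32 + 0.20)/2 = 0.26.

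n = [1.96·√(2·0.26·0.74) + 0.842·√(0.32·0.68 + 0.20·0.80)]² / 0.12² → 209 per group.

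209 × 1.2 = 251, within 3% of the stated 245 (with unpooled variance, 206 × 1.2 → 248). So 245 is reproduced approximately, on a rate that applies to patients who have already withdrawn. Power is 86.0% if all 245 per arm stop and are evaluable, and 77.5% with 196 (a 20% loss).

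**2. The passages side by side.** For a patient who relapses at, say, week 48:

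- Statistics analysis: in the analysis set, because randomised.
- Therapeutic regimen: out of the study, so no off-therapy data.
- Primary outcomes and Outcome analysis: cannot have the event, because it is defined after withdrawal.
- Missing data: no off-therapy ALT or HBV DNA, hence excluded from the primary analysis.

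Two readings remain. If the patient is dropped, the intention-to-treat statement is not met. If the patient is kept, a treatment failure is scored as recurrence-free. The same conflict arises for a patient who does not meet the stopping criteria or declines the second consent.

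**3. Possible bias when patients are dropped.** The documents give no filter rates, so all inputs except 32% are assumptions. Suppose true off-therapy risk is 32% in both arms and one arm loses an extra share x of patients whose risk is r. Its observed rate is (0.32 − x·r)/(1 − x).

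| r | x = 5% | x = 10% |
|---|---|---|
| 32% | 32.0% | 32.0% |
| 50% | 31.1% | 30.0% |
| 80% | 29.5% | 26.7% |
| 100% | 28.4% | 24.4% |

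At r = 80% the shift is 2.5 or 5.3 points (5.3/12 = 44% of the target difference). If the experimental arm loses these patients, the shift is a spurious benefit. If the control arm loses them, a true 32% vs 20% with x = 10% reads 26.7% vs 20.0%, or 6.7 points.

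A second illustration, also on assumed rates: on-treatment relapse 5% (control) vs 15% (experimental), then 32% vs 24% off therapy. The planned comparison shows an 8-point benefit. Over all randomised patients the totals are 0.05 + 0.95 × 0.32 = 35.4% and 0.15 + 0.85 × 0.24 = 35.4%, so there is no difference.

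**4. Power when everyone randomised is counted.** 245 per arm, 32% vs 20% among those who stop, equal share s not stopping in both arms (s assumed):

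| s | Non-stoppers have no event | Power | Non-stoppers counted as failures | Power |
|---|---|---|---|---|
| 5% | 30.4% vs 19.0% | 83.5% | 35.4% vs 24.0% | 79.0% |
| 10% | 28.8% vs 18.0% | 80.8% | 38.8% vs 28.0% | 71.8% |
| 15% | 27.2% vs 17.0% | 77.8% | 42.2% vs 32.0% | 64.8% |
| 20% | 25.6% vs 16.0% | 74.6% | 45.6% vs 36.0% | 58.0% |

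The first pair of columns uses rates 0.32(1 − s) and 0.20(1 − s). The second adds s to each.

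**The case against.** **The bias may be small.** Both arms take entecavir throughout, the Discussion calls resistance to it low, and the introduction says traditional Chinese medicine alone has no explicit antiviral effect. On-treatment relapse may be rare and similar in both arms, and the bias is then small. This stands as a limit on size. The protocol neither ensures it nor gives a rate to support it.

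**Blinding protects the discretionary filters.** With matched placebo and concealed allocation, re-consent, deviations and investigator discretion should not differ through knowledge of the arm. That is right, but they can still differ through a real effect or tolerability, and blinding does nothing about the ALT and HBV DNA filters.

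**An unseen plan may settle the counting.** How removed patients are scored could be specified elsewhere, and the flowchart is not available. But the conflict lies between rules the article states, and removal from the study ends data collection whatever an analysis plan says.

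**A stronger reading that does not hold.** A reader might infer from the abstract, "The primary outcome is the cumulative rate of CR at the end of this trial", that the abstract counts on-treatment relapses and so contradicts the main text. It does not say from randomisation. It introduces clinical recurrence after the sentence on stopping, as the event that leads to entecavir being restarted, which presupposes a patient who is off it. In context it agrees with the Primary outcomes section. Counting from randomisation is a proposal made here, not the protocol's own definition.

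**Conclusion.** The concern holds. The stated intention-to-treat analysis of all randomised patients cannot be delivered for an outcome observable only after withdrawal, given the removal of on-treatment relapsers, the stopping criteria, the second consent and the exclusion of incomplete off-therapy cases. The abstract and Therapeutic regimen also disagree on who stops, so the risk set is not settled. These conclusions need no assumed figure.

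The size and direction of the bias are unknown. The 2.5- and 5.3-point shifts depend on an assumed extra loss of 5% or 10% and an assumed 80% risk, and vanish if those lost have average risk. A reader might infer that the design favours the experimental arm. The documents do not support that: if the granules help during consolidation, more marginal patients may reach withdrawal and the bias would run against them. Nor is it established that patients not meeting the criteria never stop; Therapeutic regimen implies it, but the abstract says otherwise.

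**What to change.** 1. Define the primary outcome for every randomised patient as clinical recurrence from randomisation to week 120, with clinical relapse during consolidation counted as an event.
2. Replace removal from the study by discontinuation of study treatment, with ALT and HBV DNA still collected at the scheduled visits to week 120. Do the same for withdrawals for deviation or investigator discretion. This concerns data collection only.
3. Analyse patients who do not stop on their observed recurrence status. As sensitivity analyses, count them as failures, and exclude them.
4. Delete the Missing data exclusion from the primary analysis.
5. Present off-therapy-only recurrence among those who stop as supportive, and report non-stoppers by arm and reason.
6. Reconcile the abstract with Therapeutic regimen on who discontinues.

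**Cost.** Changes of wording, and follow-up of patients who would otherwise leave, at visits already scheduled. The main estimate becomes the effect of the whole strategy and not of post-withdrawal recurrence alone. Power must be restated for the new outcome: about 81% or 75% at 245 per arm if 10% or 20% do not stop and have no event, and about 72% or 58% if they count as failures. That loss is why counting every non-stopper as a failure is better kept as a sensitivity analysis; it would also put a declined consent on a par with clinical relapse.
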